## Abstract

**Background:**

Physical activity (PA) has been identified as a central component in the promotion of health. PA programs can provide a low cost intervention opportunity, encouraging PA behavioral change while worksites have been shown to be an appropriate setting for implementing such health promotion programs. Along with these trends, there has been an emergence of the use of pedometers as a self-monitoring and motivational aid for PA.

This study determines the effectiveness of a worksite health promotion program comprising of a 10-week, pedometer-based intervention (“*Steps that Count!*”), and individualized email-based feedback to effect PA behavioral change.

**Methods:**

The study is a randomized controlled trial in a worksite setting, using pedometers and individualized email-based feedback to increase steps per day (steps/d). Participant selection will be based on attendance at a corporate wellness event and information obtained, following the completion of a Health Risk Appraisal (HRA), in keeping with inclusion criteria for the study. All participants will, at week 1 (pre-intervention), be provided with a blinded pedometer to assess baseline levels of PA. Participants will be provided with feedback on pedometer data and identify strategies to improve daily PA towards current PA recommendations. Participants will thereafter be randomly assigned to the intervention group (INT) or control group (CTL). The INT will subsequently wear an un-blinded pedometer for 10 consecutive weeks.

Individualized feedback messages based on average steps per day, derived from pedometer data (INT) and general supportive/motivational messages (INT+CTL), will be provided via bi-weekly e-mails; blinded pedometer-wear will be conducted at week 12 (post-intervention: INT+CTL).

**Discussion:**

The purpose of this paper is to outline the rationale behind, and the development of, an intervention aimed at improving ambulatory PA through pedometer use, combined with regular, individualized, email-based feedback. Pedometer-measured PA and individualized feedback may be a practical and easily applied intervention.

**Trial registration:**

Number: DOH-27-0112-3951

## Background

Physical inactivity is a global health concern. Despite the awareness of physical inactivity, solutions to the problem are complex, as behavioral change is often difficult to achieve and, more importantly, to sustain. Small behavioral changes may, however, be more feasible to achieve and to maintain, the impact of which may be significantly beneficial towards improved clinical outcomes and overall well-being [1]. The work-site is an appropriate setting to initiate health promotion (HP) intervention programs where social and cultural disparities can often be overcome through the shared interest of well-being [2]. A critical review [3] identifying the effectiveness of work-site physical activity programs on physical activity, physical fitness, and health showed support towards the implementation of worksite physical activity programs to increase the habitual levels of physical activity (PA) among employees.

In South Africa (SA), a large proportion of the working population can be reached through health risk appraisals (HRA’s), conducted by health insurers [4]. This voluntary appraisal typically consists of anthropometric measures (such as body mass index (BMI) and waist circumference); clinical measures (such as blood glucose and blood cholesterol concentrations, blood pressure (BP)) and information related to health risk behavior, including physical activity (PA) and readiness for change. Similar HRA’s are administered in other countries such as the Netherlands [5] and Denmark [6] and more recent studies have adopted this approach as part of an intervention to evaluate the effectiveness of HRA’s and follow-up support [7,8].

The emergence of pedometers as a useful self-monitoring and feedback tool and therefore a useful motivational aid for increasing PA [9,10] has complemented behavioral change strategies with the objective of increasing PA. Researchers have acknowledged that in terms of practicality, pedometers offer a good solution for a low cost, objective monitoring and behavioral modification tool and a practical aid for PA interventions [11-14]. Pedometers have therefore gained popularity for use in PA interventions in various settings [15] to facilitate behavioral change.

Providing individualized feedback has been promoted as a useful adjunct to many health and well-being interventions and has often been used as an additional support measure to pedometer-based interventions [16]. A number of on-site and face-to-face programs have been found to be effective [3,17]. There is, however, a large gap between the development of effective interventions and their feasibility for use in public health practice [18,19]. A primary limitation is the high cost and large time demands on both staff and participants [19]. Using lower cost intervention strategies, such as pedometer-based approaches supplemented by email-based feedback, may have the potential to overcome this limitation. Also, an attempt at evaluating the benefits of short-term interventions (such as a 10 week intervention) may be useful in identifying whether significant changes in PA behavior can be achieved within this time-frame.

This study provides an opportunity to evaluate the effect of a pedometer-based intervention complemented by individualized, email-based feedback in improving PA in an employed population.

### Aim

To develop a 10-week, pedometer intervention*- “Steps that count!”-* that examines the effectiveness of pedometer use complemented by individualized, email-based feedback on daily PA levels, in an employed South African population.

## Methods

The proposed study is a randomized controlled study on the effectiveness of “*Steps that count!”* in a worksite setting, primarily using pedometers and feedback messages through regular, bi-weekly emails.

The concept of *“Steps that count!”* is developed from the findings of 2 recent studies that identify and highlight the importance of intensity of steps accumulated [20,21]. This (intensity-based steps) outcome complements other recent pedometer-based studies that have identified and recommended steps/min rates for moderate physical activity (MPA) [14,22-24]. A pilot feasibility study recently conducted [25], using a similar methodology, has further informed the development of this intervention and sample size calculation. The term “S*teps that count!”,* and the intervention presented has therefore been adopted as a term and a strategy for engaging people into accumulating intensity-based steps, and forms a key element of the intervention.

The behavioral strategies underlying “*Steps that count!”* include certain principles from several behavioral theories such as the theory of planned behavior and reasoned action [26,27], which proposes that a person’s intention to perform a behavior is the central determinant of performing that behavior. In addition, the Transtheoretical Model (TTM) [28], developed as an explanatory framework for intentional behavioral change, is based on the observation that people tend to move through a series of stages (pre-contemplation, contemplation, preparation, action and maintenance) in their attempt to change a certain behavior [29]. This intervention is specifically targeted at individuals in the contemplation phase of the TTM, i.e. individuals considering change even though they may be ambivalent about changing.

The intervention is not designed to test any particular theoretical model, but rather to incorporate elements from these models to initiate and sustain behavioral change. These behavioral strategies will be applied in a basic structure to improve PA by providing cues and repetition that help make the new behaviors habitual (Figure 1). Following the baseline pedometer wear, “*Steps that count!”* promotes and reinforces the intention to change PA behavior, through feedback on PA from the pedometer data, a brief discussion around current PA recommendations, and identifying possible strategies to improve steps/day. The intervention attempts to motivate an increase in PA by requesting commitment to small achievable goals, such as “adding 10 minutes of ‘*steps that count’* to your day” or “increasing daily steps by 10% per week until 30 minutes of *‘steps that count’* are achieved”. Individual PA patterns are summarized and presented, PA recommendations reinforced and some options as to how to increase PA levels are provided in the emailed feedback.

**Figure 1 F1:**
[figure not shown]
Flow of the study design.

### Study setting and study population

The study will be conducted at selected worksite settings that are based in the province of KwaZulu-Natal, RSA. The organization will offer and conduct a HRA to employees attending the wellness event. The HRA will identify cardiovascular risk factors (including: family history, dietary intake behavior, smoking and stress), and biometric measures will include BMI, %BF, BP, blood glucose and blood cholesterol concentrations. In addition, self-reported PA as well as intention for change towards improved PA will be assessed. After completion of the HRA, employees will be invited by the researcher and/or assistant to participate in the study (subject to meeting the relevant inclusion criteria). All employees eligible to participate in the study will be requested to wear a blinded pedometer for 7 consecutive days as a baseline measure of PA.

### Sample size, recruitment and randomization

We estimated sample size on the basis of aiming to show an improvement of 2,500 steps/d (and a baseline value of 7,500 steps/d) with an approximate standard deviation of ±3,000 steps/d (as established through recently published papers and systematic reviews of pedometer-based interventions conducted from 1966–2007 [30-32], as well as using the outcomes from recent pedometer studies conducted in RSA [20,25]). A sample size of 30 participants per arm of the study is required to ensure 80% statistical power and with a p-value set at <0.05. However, if a modest improvement of 1 500 steps/d is considered, a sample size of approximately 85 participants per arm is required. Considering this possibility and the likelihood of performing sub-group analyses of the data based on factors such as age and gender, a sample size of 150 participants in the INT and CTL respectively would be an appropriate estimate to account for these factors.

In order to achieve this, 1200 employees attending wellness events will be targeted. Of these, a minimum of 480 employees (40%) will be identified to be in the contemplation stage of TTM [33]. On an assumption that at least eighty percent (N=385) will agree to participate (as in the contemplation stage of TTM for PA), of which approximately 90% (N=345) will complete a 3 day blinded pedometer wear [34], 175 participants will be randomly assigned to the INT and wait-listed CTL respectively. An expected 15-20% loss to follow-up [5,35] will result in a final number of approximately 150 per arm of the study for analyses.

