### Testing protocol

All eligible employees who sign the informed consent will be required to wear a blinded pedometer (Omron HJ 720 ITC) for 7 days during week 1 and week 12 of the study. Upon return of the pedometer (after week 1), steps/d data will be electronically downloaded by the researcher according to the Omron Health Management Manager software protocol [37] and feedback (in terms of average total steps/d and information relating to moderate intensity steps (*“steps that count”*)) will be provided to each participant. Simple messages to improve PA levels will be discussed in keeping with the PA recommendation of 30 minutes of moderate PA (MPA) at least five times a week [38]. Participants will be encouraged to improve their PA levels steadily (for example by 10% per week until 30 minutes of MPA is achieved) during the subsequent 10 weeks. They will then be randomly allocated to an INT or wait-listed CTL and participants in the INT will be provided with an un-blinded pedometer for the subsequent 10 weeks. Those included in the INT will be guided as to how to download their pedometer data and its interpretation. (A 1-page step by step guideline will be provided and participants will be advised to contact the researcher for assistance, if need be). Participants will be advised to download data whenever suitable (This would provide the researcher with information as to how often the downloading feature was accessed).

Following the blinded pedometer wear at week 12 (INT and CTL), an HRA similar to the initial HRA will be conducted. The results obtained (HRA information and pedometer data) will then be compared with the information obtained in week 1 to establish the intervention effect. Participants in the CTL will be offered the pedometer intervention after the HRA conducted at 12 weeks.

Figure 1 provides a flow diagram of the randomized controlled trial intervention plan.

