### Intervention content

Pedometer data will be requested (via e-mail) from the INT at bi-weekly intervals. INT participants will be provided with individualized, emailed feedback and a general pamphlet on ways to increase PA following the bi-weekly receipt of pedometer data, via email. The CTL will similarly be provided with the general pamphlet (as in the INT) at bi-weekly intervals.

The individualized feedback (provided only to the INT) will include information on the average daily steps/d accumulated, the number of days (if any) that aerobic steps were accumulated, and the volume thereof in the form of a personalized email. The feedback will also include information such as the highest number of steps/d accumulated by the individual over the past two weeks and the category within which the average steps/d fall, as per current steps/day categorizations [22,23,42] (Figure 2). Participants will be encouraged to steadily increase their steps by approximately 10% per week until the target of at least 30 minutes of aerobic steps (displayed as “orange” steps on the pedometer download) is achieved and/or maintained by the end of the intervention.

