## Discussion

The purpose of this paper is to outline the rationale behind, and the development of, an intervention aimed at improving the daily PA in a South African employed population, and to describe the study protocol evaluating its effect.

A recent literature review identified thirty studies using web-based interventions to increase weight loss and/or PA [43]. Twenty-eight of the studies (93%) reported positive changes in moderate to vigorous PA level, fruit and vegetable intake and psychological factors [43]. The review suggests that web-based interventions are a useful educational tool for increasing awareness and making healthy behavior changes. The self-maintained improvement of PA and maintenance thereof is a further aspect that can also be monitored and evaluated over regular time intervals.

There are limitations that must be noted in the study design. Firstly, there is an element of selection bias as the study will involve selection from a convenience sample of persons who are recruited as a result of attending a corporate HRA. Secondly, the general information provided to both the INT and CTL is the same irrespective of individual progress toward improved PA. Also, the CTL receives the same general motivational messages as the INT, bi-weekly, which may lead to increased PA in the CTL and a resultant weakened effect of the intervention. A further limitation is that the pedometer will be used as a measurement tool (albeit blinded for measurement at weeks 1 and 12, respectively) and during the 10 week intervention.

The study has strengths that can be noted. To our knowledge, this will be the first pedometer-based intervention conducted in SA (other than the pilot feasibility study conducted) and will provide useful information regarding potential for PA improvements through pedometry in an adult working group. This is the first pedometer-based intervention, to our knowledge, that takes into account intensity and duration of PA during free-living wear to provide information on patterns of PA in an employed, adult population. The study will, therefore be useful for further pedometer-based intervention initiatives that can be applied in other contexts and settings on a larger scale.

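### The sample-size target does not say whether it is the intervention arm's gain or the between-arm difference, allows nothing for control-arm gain, and attaches 80% power to sample sizes that give about 90%

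*Protocol article*

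**What the plan says.** All references are to the protocol article.

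- **Sample size, recruitment and randomization.** The planning effect is given as "aiming to show an improvement of 2,500 steps/d (and a baseline value of 7,500 steps/d) with an approximate standard deviation of ±3,000 steps/d". The first result is: "A sample size of 30 participants per arm of the study is required to ensure 80% statistical power and with a p-value set at <0.05". The second is: "if a modest improvement of 1 500 steps/d is considered, a sample size of approximately 85 participants per arm is required". The section then adopts 150 analysed per arm (175 randomised, 15-20% loss). Its reasons are the smaller effect and likely sub-group analyses by factors such as age and gender. No control-arm change is stated.
- **Testing protocol.** After the week 1 wear and before allocation, every participant receives feedback on their steps and a discussion of the activity recommendation. "Participants will be encouraged to improve their PA levels steadily (for example by 10% per week until 30 minutes of MPA is achieved", and randomisation follows.
- **Intervention content.** "The CTL will similarly be provided with the general pamphlet (as in the INT) at bi-weekly intervals".
- **Discussion.** The messages sent to controls are listed as a limitation "which may lead to increased PA in the CTL and a resultant weakened effect of the intervention".
- **Statistical analyses.** The week 12 value is regressed with adjustment for the baseline value, and arms are compared as allocated.

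**The concern.** A baseline-adjusted comparison of week 12 steps estimates only the difference between arms. Any gain that both arms share cancels out. The target is worded as an improvement and paired with a starting level of 7,500 steps/d, which reads naturally as change from baseline in the treated group. On that reading, the sizing equals the between-arm effect only if controls do not change. Yet these controls are people contemplating change who receive feedback, encouragement and repeated messages, and the article itself expects that some of this may raise their activity.

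Two things are at stake. A reader cannot tell which difference the trial was powered for. And if the net difference turns out small, a null result could be taken to mean that the pedometer with individual feedback does not work, when the sizing never addressed the net effect.

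**Working it through.** **Inputs from the article:** effects of 2,500 and 1,500 steps/d; SD 3,000; significance level 0.05; stated power 80%; stated n of 30 and about 85 per arm; adopted n of 150 per arm; 175 randomised with 15-20% loss, so 175 × 0.85 = 149 down to 175 × 0.80 = 140.

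**Assumptions:** the test is two-sided (not stated), and SD 3,000 is the SD of the analysed value (the article does not say whether it refers to level or change). Control gains are assumptions throughout, since no figure is given.

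**Step 1. Reproduce the stated n.** For two means, n per arm = 2 × (SD/difference)² × (z for alpha + z for power)².

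- 2,500 at 80%: 2 × (3,000/2,500)² × (1.960 + 0.842)² = 2 × 1.44 × 7.85 = 22.6, so 23 (24 with the t distribution).
- 1,500 at 80%: 2 × (3,000/1,500)² × 7.85 = 62.8, so 63 (64 with t).
- At 90%, (1.960 + 1.282)² = 10.51: 2 × 1.44 × 10.51 = 30.3 and 2 × 4 × 10.51 = 84.1, so 31 and 85.

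The stated 30 and 85 therefore match 90% power, not 80%. By t-test, power is 89% at 30 per arm for 2,500 and 90% at 85 per arm for 1,500. Other explanations fit less well:

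- Inflating the 80% figures for 20% loss gives 29-30, which fits the first figure, but only 79-80 for the second.
- A one-sample or paired calculation at 80% gives 14 and 34.
- An SD of about 3,460-3,490 would give 80%, but the article states 3,000.
- A one-sided test at 95% power comes close (32 and 87), but is further from the text.

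**Step 2. Difference detectable with 80% power.** Difference = SD × √(2/n) × 2.80, with the t correction:

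| n per arm | Detectable difference (steps/d) |
|---|---|
| 30 | about 2,207 |
| 85 | about 1,297 |
| 140 | about 1,008 |
| 150 | about 974 |

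**Step 3. Control gain that can be absorbed, if the stated improvement is the intervention arm's gain.** Tolerated control gain = intervention gain − detectable difference.

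- 30 per arm, gain 2,500: 2,500 − 2,207 = about 290.
- 85 per arm, gain 1,500: 1,500 − 1,297 = about 200.
- 150 per arm, gain 2,500: 2,500 − 974 = about 1,525.
- 150 per arm, gain 1,500: 1,500 − 974 = about 525.

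**Step 4. Illustrative control gains.** Two amounts can be scaled from the article's own goals. Ten minutes of counted steps at 60 per minute is 10 × 60 = 600 steps/d. One 10% increment on 7,500 is 750 steps/d. These are goals, not evidence of what controls will achieve. Power by t-test, SD 3,000:

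| Intervention gain | n per arm | Control gain 0 | 600 | 750 |
|---|---|---|---|---|
| 2,500 | 30 | 89% | 67% | 60% |
| 1,500 | 85 | 90% | 49% | 37% |
| 2,500 | 150 | >99% | >99% | >99% |
| 1,500 | 150 | 99% | 74% | 58% |

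**Step 5. Effect of baseline adjustment.** With an assumed baseline to week 12 correlation of 0.5, the residual SD is 3,000 × √(1 − 0.25) = 2,598. At 150 per arm, the detectable difference falls to 974 × 0.866 = about 845. The last row's 74% and 58% become 85% and 70%.

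**The case against.** A reader might infer that the trial was sized on a static control, so that its power statement does not apply to the between-arm test. The article does not support that. It never states zero control gain and never says that 2,500 is a within-arm change. It gives n per arm, and 30 and 85 fit a two-sample formula (at 90% power) far better than a one-sample or paired one. If 2,500 and 1,500 are already between-arm differences, the sizing does address the planned test. The cited reviews and the pilot may also have reported effects against controls; the article does not settle this.

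A reader might also infer from the steep falls at 30 and 85 per arm that the trial is underpowered. Those are not the sizes adopted. At 150 per arm, power for a 2,500 gain stays above 99% under both illustrative control gains. A shortfall requires the smaller intervention gain together with a control gain above about 525 steps/d, and baseline adjustment, which is planned, would soften it. Nor is the smaller effect ignored: planning for 1,500 and then going from 85 to 150 leaves real reserve, though control gain is not given as a reason for it.

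These arguments limit the point but do not remove it. The target remains ambiguous, the dilution acknowledged in the Discussion is not carried into the sizing, and the 80% figure does not follow from the stated inputs on the two-sample reading.

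**Conclusion.** The point holds in limited form, at minor to moderate severity. The article does not define its target as a within-arm gain or a between-arm difference, and it allows nothing for a control gain that it regards as possible. If the target is the intervention arm's gain, the 80% claimed for 30 and 85 per arm survives only small control gains. The main comparison at 150 per arm is adequate unless the net difference falls below about 975 steps/d (about 1,010 at 140 per arm). Separately, as a two-sample calculation the stated n carry about 90% power.

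These results rest on SD 3,000, a two-sided 0.05 test and, for the detectable differences, no credit for baseline adjustment. The actual control gain is unknown, so whether a shortfall would arise cannot be determined from the article.

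**What to change.** Keep the design and the 150 per arm, and rewrite the sample-size paragraph.

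1. State the target as a between-arm difference in week-12 steps/d, net of the assumed control change, and say which SD is meant. Suggested wording: with 140-150 analysed per arm, SD 3,000 and two-sided 0.05, the trial has 80% power for a net intervention-control difference of about 975-1,010 steps/d, and for a smaller one with baseline adjustment.
2. Replace the 80% attached to 30 and 85 per arm with about 90% for a between-arm difference, or drop that statement. Labelling it as assuming an unchanged control arm is not enough, because 30 and 85 would still not be the n for 80% power.

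The cost is rewording only, with no added participants or procedures. The downside is that the reserve shown for the 1,500 steps/d scenario becomes less favourable.

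### The stated 30 and about 85 participants per arm do not follow from the stated inputs at 80% power, which give 24 and 64; the error is conservative and the correction is minor

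*Protocol article*

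**What the plan says.** All the figures are in the Protocol article, Methods, under Sample size, recruitment and randomization. The first scenario is an improvement of 2,500 steps/d from a baseline of 7,500, "with an approximate standard deviation of ±3,000 steps/d". The conclusion drawn is: "A sample size of 30 participants per arm of the study is required to ensure 80% statistical power", "and with a p-value set at <0.05". The second scenario follows directly: "if a modest improvement of 1 500 steps/d is considered, a sample size of approximately 85 participants per arm is required". That sentence gives no power, SD or significance level of its own, so the natural reading carries over 80%, 3,000 and 0.05.

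The article then settles on 150 per arm, citing the smaller effect and likely sub-group analyses. Loss to follow-up is handled at a separate step: "175 participants will be randomly assigned to the INT and wait-listed CTL respectively", and "An expected 15-20% loss to follow-up [5,35] will result in a final number of approximately 150 per arm of the study for analyses".

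**The concern.** Effect, SD, significance level, power and size are printed side by side, so the statement can be checked from the article alone. It fails the check: both sizes are well above what the inputs require at 80% power, and both fall close to the 90% sizes. At least one printed quantity (the power, the SD or the sizes) is therefore not the one used.

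What is at stake is the accuracy of the planning statement and its reuse. A reader cannot tell whether the power is mislabelled or whether a larger SD lies behind the sizes. Anyone borrowing the SD or the sizes for a similar pedometer trial would inherit the inconsistency. The trial's ability to answer its question is not at stake.

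**Working it through.** **Inputs, all from the sample size section.** Difference d = 2,500 or 1,500 steps/d; SD s = 3,000; alpha 0.05; power 80%; two arms of equal size. Sidedness is not stated, so two-sided is assumed and one-sided is tried below.

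**Normal approximation.** n per arm = 2 × (z for alpha + z for power)² × (s/d)².

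- (s/d)² = (3,000/2,500)² = 1.44, or (3,000/1,500)² = 4.
- 80% power: (1.960 + 0.842)² = 7.849. For 2,500: 2 × 7.849 × 1.44 = 22.6, so 23. For 1,500: 2 × 7.849 × 4 = 62.8, so 63.
- 90% power: (1.960 + 1.282)² = 10.507. For 2,500: 2 × 10.507 × 1.44 = 30.3, so 31. For 1,500: 2 × 10.507 × 4 = 84.1, so 85.

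**Exact two-sample t-test (noncentral t), two-sided 0.05, SD 3,000.**

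| Difference | Stated n per arm | n for 80% | n for 90% | Power at stated n |
|---|---|---|---|---|
| 2,500 | 30 | 24 | 32 | 88.8% |
| 1,500 | about 85 | 64 | 86 | 90.0% |

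The excess over the 80% size is 30/24 = 1.25 and 85/64 = 1.33. Rounding does not account for that.

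**Attempts to reproduce both stated sizes at 80% power.**

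- One-sided 0.05: 19 and 51 per arm by t-test, which is further away.
- Loss to follow-up already included: 24/0.85 = 28.2 and 24/0.80 = 30; 64/0.85 = 75.3 and 64/0.80 = 80. A 20% loss would explain 30 but not 85. About 25% would be needed for 85 (64/0.75 = 85.3), which is outside the article's range. The article also applies its loss separately, from 175 to about 150.
- Baseline adjustment, as planned under Statistical analyses: this lowers the required size and widens the gap. With an assumed correlation of 0.5, the normal approximation gives 17 and 48.
- Single-group paired comparison: 12 and 32.
- Larger SD: the t-test has exactly 80% power at 30 per arm with SD about 3,400, and at 85 per arm with SD about 3,470.
- Change scores, with 3,000 as the SD at a single time: a correlation near 0.33 gives a change SD of 3,000 × √(2 × 0.67) ≈ 3,470, close to both stated sizes. The article gives no correlation, and its planned model regresses the follow-up value on baseline rather than analysing change.

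No standard calculation using only the documented inputs gives both sizes at 80%.

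**Consequence for the adopted size.** At 150 per arm, SD 3,000 and d = 1,500, power is 99.1%. At 140 per arm (175 × 0.80, the upper end of the expected loss) it is 98.6%. Even with SD 3,470, power at 150 per arm is about 96%.

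**The case against.** The best defence is that the SD is given only as approximate. A value of 3,400 to 3,470 rounds to 3,000 at the nearest thousand and would make both sizes roughly right at 80%. The sources for the SD are cited but not at hand, so this cannot be excluded. It stands as a possible explanation. It does not rescue the text as printed, because 3,000 is the only SD reported and the sizes are not what it yields.

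The same point limits the diagnosis. A reader might infer that the authors calculated at 90% and mislabelled the result. The fit is close, but 30 per arm falls short of 90% (88.8%; 32 would be needed), and the documents do not show what was run.

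A reader might also infer that the error feeds into the final sample size. The article does not compute 150 from 85. It presents 150 as a judgement that allows for the smaller effect and for sub-group analyses, and replacing 85 with 64 would leave it unchanged.

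It is also fair to say that 80% is written only in the 30-per-arm sentence. Its application to the second scenario is a natural reading, not an explicit statement.

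Finally, the unstated sidedness, an SD not reduced for baseline adjustment and the absence of a detectable difference at the analysed size are not faults here. They are details that an article may leave to the full protocol or SAP, and an unreduced SD is an ordinary conservative choice.

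**Conclusion.** The point holds as a minor correction of a stated figure. On the article's own inputs, 80% power needs 24 and 64 per arm, not 30 and about 85; the stated sizes give about 89% and 90%. This rests on a two-sided, between-arm comparison of means with SD 3,000, and on carrying 80% over to the second scenario. The one-sided alternative makes the discrepancy larger.

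It would be wrong to conclude that the trial is underpowered or that its design must change. The article asks for more participants than its inputs require, and the adopted 150 per arm far exceeds either figure.

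**What to change.** Reconcile power, SD and sizes in the sample size section in one of three ways, according to what was actually calculated:

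1. If the intended power was about 90%, say so, with 32 and 86 per arm by t-test; or keep 30 and 85 and describe their power as about 89-90%. Changing only the percentage to exactly 90% would leave the 30-per-arm sentence slightly wrong.
2. If 80% was intended with SD 3,000, restate the sizes as 24 and 64 per arm.
3. If a larger SD, or a change-score SD based on an assumed correlation, was used, report that value in place of 3,000.

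The cost is a few words. Enrolment, the target of 150 per arm and the planned analysis stay as they are.
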